#### Exploratory outcomes

Height adjusted liver volumes, compared between the direct and delayed start group after 18 monthsEstradiol, progesterone, AMH, LH and FSH levels at baseline, 6, 18, 24 and 36 monthsDifference between acute and chronic effects of treatment on liver growth as assessed by a mixed models analysis comparing liver growth rate in the first 6 months of treatment compared to the next 12 months of treatment.
With respect to tolerability:Quality of life, using the validated 36-Item Short Form Health Survey (SF-36) and the Beck Depression Inventory II (BD-II) questionnairesMenopause related complaints: using the Menopause Specific Quality of Life (MENQOL) questionnaireBone density: T-score on Dual Energy X-ray Absorptiometry (DEXA) scans will be compared between direct start group and delayed start group after 18 months.
For patients with polycystic kidney disease (PKD) also:Kidney growth (%/y) calculated over the first 18 months of the trial compared between direct and delayed start groupKidney growth rates within individuals compared before treatment and during treatmentDifferences between acute and chronic effects of treatment on kidney growthRenal function decline before and during treatment.

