### Randomization

Participants will be randomized 1:1 between direct and delayed start (after 18 months) of treatment using an online Interactive Response System (IXRS) tool, stratified for somatostatin analogue use (yes/no) and age (< 40 and ≥ 40 years).

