### Outcome parameters

#### Primary outcome

Liver growth (%/y), calculated over the first 18 months of the trial and compared between the direct start group (on treatment) and delayed start group (on standard of care), b–e versus b–c, Fig. 3.

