#### Secondary outcomes

Change in PLD disease severity, assessed by the validated PLD-Q questionnaire, calculated over the first 18 months of the trial and compared between the direct start group (on treatment) and delayed start group (on standard of care).Liver growth rates within individuals compared before treatment and during treatment. In the direct start group, historical growth rates (Fig. 3a, b) will be compared with growth rate during 18 months of treatment (b–e) and in the delayed start group, growth rates during the first 18 months of the trial (untreated, b–c) will be compared with the last 18 months of the trial (treated, c–d).The incidence of (serious) adverse events, compared between the direct and delayed start group in the first 18 months of treatment.

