## Data collection and management

The study consists of one or two screening visits, nine hospital visits and one phone call. During short visits (3, 12, 15, 21 months), a small set of local laboratory measurements, vital signs, AEs and concomitant medication will be assessed. At larger visits (BL, 6, 18, 24 and 36 months) in addition MRI scans, extensive lab and questionnaires will be performed. DEXA scans are made at baseline, halfway and end of the study (Figs. 3, 4). Data will be entered in a web-based electronic case report form to ensure correct and timely data collection in a central database.

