### MRI scans

Liver and kidney volumes (the latter in ADPKD patients only) will be measured using an MRI scan at screening, 6, 18, 24 and 36 months. MRI scans will be performed using a standardized protocol, including a coronal T2-weighted single-shot fast gradient spin-echo sequence with fat-saturation with a slice thickness of 3 mm which is the primary sequence to determine liver volumes. In addition, a transversal T2-weighted single shot fast gradient spin-echo sequence with fat suppression and a coronal T1-DIXON-VIBE spoiled gradient echo sequence will be obtained. After pseudonymization, MRI scans will be sent to the central reading facility, where images will be analyzed blinded for patient, time and treatment by trained observers using an automated MRI program [30]. To ensure that valid MR images are obtained, quality control will be performed within 72 h by trained personnel. In case a scan is rejected, it will be repeated.

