### Statistics

#### Statistical analysis

Analyses are performed after completion of the study. For the primary outcome, liver growth during the first 18 months of the trial compared between direct and delayed starters, an unpaired t-test will be used. In case of missing data, last information will be used adjusted for the duration of follow up. For questionnaires, the delta in scores during the first 18 months of the trial will be compared between direct and delayed starters. To compare liver growth within individuals before and during treatment, a paired t-test will be used. Adverse events will be categorized and the number of adverse events per category will be compared between direct and delayed starters using an unpaired t-test.

For all primary and secondary analyses, we will perform pre-defined sensitivity analysis to adjust for age, disease type (ADPKD vs. ADPLD), total liver volume at baseline, total kidney volume at baseline, use of somatostatin analogues, and test differences in treatment effects among these variables (interaction). In a sensitivity analysis we will test for differences in the outcome variables between the first 18 months of the trial and the second 18 months of the trial in the direct start group, using a breakpoint analysis. All analyses will be performed based on an intention to treat principle. As a sensitivity analysis, we will perform a per-protocol analysis.

In an additional analysis we will explore whether liver growth is linear and whether the liver growth rate during treatment is different in the first 6 months of treatment compared to the 12 months thereafter, using a multiple mixed model.

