On the longer term, estrogen depletion could lead to an increased risk of osteoporosis and a slightly enhanced cardiovascular risk [26, 35, 36]. With a treatment duration of 18 or 36 months, we do not expect large detrimental effects on the long term. However, to ensure optimal safety, patients with a history of cardiovascular disease and a low bone-density at screening will be excluded from the trial and during the trial blood pressure, cholesterol levels and bone-density will be monitored (Fig. 4). In addition, all patients will receive advise on healthy food intake and calcium and vitamin D supplementation.

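### The exploratory bone-density outcome is worded as a month-18 T-score with no stated use of the baseline DEXA; this is valid but inefficient, and free to improve

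*Protocol article*

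**What the plan says.** In the protocol article, under Exploratory outcomes, bone density is defined thus: "T-score on Dual Energy X-ray Absorptiometry (DEXA) scans will be compared between direct start group and delayed start group after 18 months". Height-adjusted liver volume, in the same section, is also compared between arms at month 18 as an attained value.

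The baseline measurements exist. Under Data collection and management, "DEXA scans are made at baseline, halfway and end of the study"; halfway through a 36-month trial is month 18. Under MRI scans, liver volume "will be measured using an MRI scan at screening, 6, 18, 24 and 36 months".

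Other outcomes are worded as changes. The primary outcome is "Liver growth (%/y), calculated over the first 18 months of the trial", and the first secondary outcome is "Change in PLD disease severity, assessed by the validated PLD-Q questionnaire, calculated over the first 18 months of the trial". Kidney growth, in the same exploratory list as bone density, is a rate over the first 18 months.

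The only covariate adjustment described, under Statistical analysis, begins "For all primary and secondary analyses, we will perform pre-defined sensitivity analysis to adjust for age, disease type (ADPKD vs. ADPLD), total liver volume at"; the liver volume meant is the baseline one, and the list goes on to baseline kidney volume and somatostatin analogue use. It does not name exploratory outcomes or baseline T-score. Randomisation is "stratified for somatostatin analogue use (yes/no) and age (< 40 and ≥ 40 years"), so baseline bone density is not a stratification factor.

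The Efficacy–safety ratio section recognises the risk: "On the longer term, estrogen depletion could lead to an increased risk of osteoporosis". It answers this with exclusion of low bone density at screening and with bone-density monitoring during the trial.

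**The concern.** Women usually differ from one another in T-score by more than one woman's T-score is likely to move in 18 months. A comparison of month-18 levels leaves all of that between-woman variation in the error term. Using each woman's own baseline value removes most of it.

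The article otherwise works with change wherever a baseline exists, so this line stands out as a stated definition and not merely a detail left out.

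At stake is one estimate. The delayed-start arm is untreated only for the first 18 months, so this is the only treated-versus-untreated randomised comparison of bone density that the article describes. If it is imprecise, a non-significant result could be read as reassurance that the data do not support.

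**Working it through.** **1. The plan's own figure.** The article gives no power figure for bone density, so the check starts from the sample size. Sample size calculation gives a difference of 5.8% per 18 months, an SD of 2 × 2.8 = 5.6%, α = 0.05 (taken as two-sided) and 80% power.

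- n per arm = 2(1.960 + 0.842)² × (5.6/5.8)² = 14.6, so 15 per arm and 30 in total.
- 30 × 1.2 = 36, which reproduces the stated 36.
- With 20% drop-out, 36 × 0.8 = 28.8 remain, about 14 per arm. Both 14 and 18 (no loss) per arm are used below.

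**2. Assumptions not in the documents.** T-score SD 0.8 to 1.2; true between-arm difference Δ of 0.5 units, with 0.3 as a smaller alternative; correlation r between baseline and month 18 of 0.8 to 0.95.

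**3. Formulas.** Two-sided t-test at 5%, noncentral t with 2n − 2 degrees of freedom and noncentrality (Δ/s)√(n/2), where s is:

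- month-18 level: SD
- change from baseline: SD√(2(1 − r)), which at SD 1.0 is 0.63, 0.45 and 0.32 for r = 0.8, 0.9 and 0.95
- month-18 value adjusted for baseline: SD√(1 − r²), which at SD 1.0 is 0.60, 0.44 and 0.31

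The one degree of freedom spent on the covariate is ignored.

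**4. Power as worded, Δ = 0.5.**

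| SD | 14 per arm | 18 per arm |
|---|---|---|
| 0.8 | 36% | 45% |
| 1.0 | 25% | 31% |
| 1.2 | 19% | 23% |

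Example: with SD 1.0 and n = 14 the noncentrality is 0.5 × √7 = 1.32, giving 25%.

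**5. Power with the baseline used, SD 1.0.**

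| Δ | n per arm | Level only | Adjusted, r = 0.8 | r = 0.9 | r = 0.95 |
|---|---|---|---|---|---|
| 0.5 | 14 | 25% | 56% | 83% | 98% |
| 0.5 | 18 | 31% | 68% | 92% | >99% |
| 0.3 | 14 | 12% | 25% | 42% | 69% |
| 0.3 | 18 | 14% | 31% | 52% | 80% |

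Change from baseline is within about 5 points of these figures (52%, 81% and 98% for Δ = 0.5, n = 14). If r were only 0.5, the change score would gain nothing over the level (25%), while adjustment would still give 31%.

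**6. Difference detectable with 80% power.** For the level it is 1.10 SD (14 per arm) or 0.96 SD (18 per arm). Multiplying by √(1 − r²), adjustment brings 1.10 down to 0.66, 0.48 and 0.34 SD for r = 0.8, 0.9 and 0.95.

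**7. Height-adjusted liver volume.** For the planned 5.8% difference and an assumed between-patient coefficient of variation of 15% to 40%, power for the month-18 level is 17% down to 7% (14 per arm) or 20% down to 7% (18 per arm).

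**The case against.** The strongest reply is that this is an outcome list in a journal article. It names a measure, two arms and a time point but no model for bone density, and nothing in it rules out using the baseline. The full protocol or SAP, not shown, may add an adjustment. That stands as a limit: the article does not say that baseline scans will be ignored. It does not dispose of the point, because the definition given is a level, other outcomes in the article are given as changes, and the stated adjustment does not reach this outcome.

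Second, a reader might infer that the comparison is biased. It is not. Randomisation makes the unadjusted comparison valid, and its standard error already allows for chance baseline imbalance. The loss is precision only.

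Third, a reader might infer that real bone loss on leuprorelin would go unseen. The documents do not support that. Bone density is monitored in individual patients, women with low bone density at screening are excluded, and a data safety board meets regularly. A large loss in one patient could be seen, and a between-arm difference near 1 SD would probably be detected.

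Fourth, SD, correlation and loss all come from outside the documents. Excluding low bone density may narrow the SD, but at 0.8 power for a 0.5-unit difference is still only 36% to 45%. Differences in scanners or reference databases between centres might be put forward as a further reason, but the documents say nothing about them and they play no part here.

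Fifth, poor power for height-adjusted liver volume does not weaken the test of the trial's main effect, since the primary outcome already starts from the baseline scan.

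**Conclusion.** The point holds as one of efficiency in an exploratory safety outcome. As worded, and assuming a true difference of 0.5 T-score units with an SD of 0.8 to 1.2, power is 19% to 36% with 14 per arm and 23% to 45% with 18. At SD 1.0, using the baseline value would at least double it for correlations of 0.8 to 0.95. The direction of the gain does not depend on the exact inputs, but its size does.

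Baseline adjustment does not guarantee detection: for a difference of 0.3 at SD 1.0, power with 14 per arm remains 25% to 69%. What is at risk is the precision of the one between-arm bone estimate described, not patient-level bone safety, the primary analysis or the sample size. The liver-volume line has the same wording problem but little consequence.

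**What to change.** Define the bone outcome as the month-18 value compared between arms with the baseline value as covariate, or as change from baseline to month 18. The covariate form is preferable because it does not lose out if the correlation is lower than expected. Reporting the difference with its confidence interval would also discourage reading a non-significant result as absence of loss.

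For consistency, word height-adjusted liver volume in the same way, with baseline height-adjusted volume as covariate. If the SAP already does this, aligning the outcome description is enough.

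The cost is wording only. The baseline DEXA and MRI scans are already scheduled, no visits or patients are added, and N = 36 is unaffected.

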### Sample size calculation

In our own DIPAK 1 trial [13], the mean liver growth rate in patients meeting the inclusion criteria was + 5.8% ± 2.8% per 18 months. Since the information on liver growth rate in this specific group is scarce, we conservatively doubled the SD to ensure enough power. We aim at fully stopping liver growth. Using β = 80%, α = 0.05, and incorporating a 20% drop-out rate, inclusion of 36 patients is needed to show this effect. In other proof-of-concept studies in PLD, similar numbers of patients were included [28, 29].

### Recruitment

Patients will be recruited from outpatient clinics of the participating centers or referred by other centers. All participating centers are expertise centers on polycystic liver and/or polycystic kidney disease and see many patients that meet the inclusion criteria for the trial. We planned 24 months for the recruitment period.

## Data collection and management

The study consists of one or two screening visits, nine hospital visits and one phone call. During short visits (3, 12, 15, 21 months), a small set of local laboratory measurements, vital signs, AEs and concomitant medication will be assessed. At larger visits (BL, 6, 18, 24 and 36 months) in addition MRI scans, extensive lab and questionnaires will be performed. DEXA scans are made at baseline, halfway and end of the study (Figs. 3, 4). Data will be entered in a web-based electronic case report form to ensure correct and timely data collection in a central database.

**Fig. 4 Fig4:**
[figure not shown]
Visit schedule. S = screening, BL = baseline, V = visit, P = phone call. Screening procedures can take place in one visit or with MRI and DEXA apart, as preferred by site and patient. Patients are randomized to direct start (at BL) or delayed start (at V5). A phone cal (P) takes place one month after first leuprorelin injection. More extensive visits with MRI, questionnares and extensive lab take place at BL, 6, 18, 24 and 36 months. Extensive lab consists also of biobanking (samples stored at − 80 °C and shipping to core laboratory for measurement of female sex hormones in one run) and in case of ADPKD, 24 h urine collection. Between visits, site personnel will remind patients to administer the leuprorelin injections by phone or email

### MRI scans

Liver and kidney volumes (the latter in ADPKD patients only) will be measured using an MRI scan at screening, 6, 18, 24 and 36 months. MRI scans will be performed using a standardized protocol, including a coronal T2-weighted single-shot fast gradient spin-echo sequence with fat-saturation with a slice thickness of 3 mm which is the primary sequence to determine liver volumes. In addition, a transversal T2-weighted single shot fast gradient spin-echo sequence with fat suppression and a coronal T1-DIXON-VIBE spoiled gradient echo sequence will be obtained. After pseudonymization, MRI scans will be sent to the central reading facility, where images will be analyzed blinded for patient, time and treatment by trained observers using an automated MRI program [30]. To ensure that valid MR images are obtained, quality control will be performed within 72 h by trained personnel. In case a scan is rejected, it will be repeated.

### Laboratory measurements

For a detailed overview of collected samples, see Fig. 4. At all visits, a limited set of laboratory measurements will be performed. At baseline and the visits at month 6, 18, 24 and 36, more extensive laboratory measurements, biobanking and in ADPKD patients, 24-h urine samples will be collected. Except form biobanking samples, laboratory samples will be analyzed locally. Biobanking samples will be stored at − 80 °C and shipped to the core laboratory at the end of the trial to measure estrogen, progesterone, AMH, FSH and LH in one run, to minimize interlaboratory and interassay variation.

### Vital signs

During every visit we will measure blood pressure, weight and abdominal circumference. Height will be collected at baseline. Upper arm circumference of the non-dominant arm will be measured every visit because this is one of the exception criteria for the MELD score [31].

### Questionnaires

Questionnaires will be sent digitally to the patient at screening, 6, 18, 24 and 36 months. Quality of life will be assessed using the SF-36 and BD-II questionnaires, PLD disease severity using the validated PLD-Q questionnaire and menopause related complaints using the MENQOL questionnaire [32, 33].

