### Intervention

Leuprorelin is a synthetical analogue of GnRH and strongly stimulates the pituitary resulting in desensitization. Thus, the production of luteinizing hormone (LH) and follicle stimulating hormone (FSH) by the pituitary stops, which leads to cessation of the production of estrogen and progesterone by the ovaries.

Leuprorelin will be started using monthly injections of 3.75 mg, and if tolerated after 3 months, treatment regimen will be switched to 3-monthly injections of 11.25 mg. Depending on patients’ preferences, participants will be trained to self-administer the injections at home or injections will be administered by study personnel.

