### Criteria for withdrawal

Subjects can leave the study at any time for any reason if they wish to do so without any consequences. Patients that drop-out from the trial within the first 3 months from baseline will be replaced and not be part of the intention to treat analysis. Patients that drop-out from the trial later on will not be replaced by new patients and will be asked for an early-end of treatment. The investigator can withdraw a subject from the study for urgent medical reasons, such as (but not limited to): occurrence of a concomitant disease in which leuprorelin is contra-indicated, pregnancy, need of treatment that is contra-indicated during the trial (such as estrogens), lost-to-follow up or, by the opinion of the treating physician, high need for surgical volume reducing treatments. If a patient that is registered on the waiting list receives a transplant offer, this patient will also be withdrawn from the trial.

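### The exploratory menopause and mood questionnaires are first repeated 6 months after leuprorelin starts, although tolerance is judged at 3 months; women who leave before month 3 have no on-treatment score and also leave the analysis set

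*Protocol article*

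**What the plan says.** The Questionnaires section fixes the schedule: "Questionnaires will be sent digitally to the patient at screening, 6, 18, 24 and 36 months". Data collection and management agrees. On the larger visits it says: "At larger visits (BL, 6, 18, 24 and 36 months) in addition MRI scans, extensive lab and questionnaires will be performed". On the others: "During short visits (3, 12, 15, 21 months), a small set of local laboratory measurements, vital signs, AEs and concomitant medication will be assessed". The visit-schedule legend (Fig. 4) also places questionnaires only at the larger visits.

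The Intervention section sets a tolerance check at 3 months: "if tolerated after 3 months, treatment regimen will be switched to 3-monthly injections of 11.25 mg". For delayed starters, who begin at month 18, the same point is month 21, also a short visit.

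Tolerability is named in the secondary objectives. The secondary outcome for it is the incidence of (serious) adverse events over 18 months. MENQOL, BD-II and SF-36 stand under Exploratory outcomes, in the part on tolerability. The Statistics section compares the change in questionnaire scores over the first 18 months between arms and applies intention to treat to all analyses.

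Criteria for withdrawal treats leavers in two ways. For early ones, on the set to be analysed: "Patients that drop-out from the trial within the first 3 months from baseline will be replaced and not be part of the intention to treat". Later ones "will not be replaced by new patients and will be asked for an early-end of treatment".

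**The concern.** The protocol expects hot flushes, mood swings and disturbed sleep, and it judges tolerance 3 months after the first injection. At that visit the instruments chosen to measure these complaints are not used. A woman who finds the drug hard to bear and leaves before month 3 contributes a pre-treatment score and nothing after it.

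In the first 18 months only the direct arm receives leuprorelin, so departures caused by the drug fall on that arm. If those women would have scored worse than the ones who stay, their absence moves the treated arm's mean in the drug's favour. The withdrawal rule adds to this, since someone else takes the place of a woman who leaves within 3 months of baseline. At stake is the symptom and mood side of the efficacy-safety ratio, on which the Discussion rests the later use of the drug.

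**Working it through.** **Who has an on-treatment score under the stated schedule**

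| Woman | Next questionnaire after start | Result |
|---|---|---|
| Direct start, leaves the trial before month 3 | Month 6 | No on-treatment score; replaced; outside the intention-to-treat set |
| Direct start, leaves between months 3 and 6 | Month 6 | None from the schedule; possibly one at the early end-of-treatment step, whose content is not stated |
| Direct start, stops the drug, stays in the trial | Month 6 | Score available, but taken off treatment |
| Delayed start, leaves between months 18 and 24 | Month 24 | As in the second row; the 3-month exclusion runs from baseline and does not apply to her |

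**Size of the shift**

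The article gives no early stopping rate and no questionnaire SD, so there is no figure of its own to reproduce on this point. The only design input is the arm size: 36 patients randomised 1:1 give 18 per arm. That total is consistent with its stated inputs. With a difference of 5.8, an SD of 2 × 2.8 = 5.6, 80% power and two-sided 5% (sidedness assumed), n = 2 × [5.6 × (1.960 + 0.842) / 5.8]² = 14.6, or 15 per arm and 30 in all. Allowing for 20% drop-out gives 30 × 1.2 = 36, or 30 / 0.8 = 37.5, rounded up to 38.

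Let k of 18 direct starters leave without an on-treatment score, and let their worsening exceed that of the others by D, in SD units. The mean over all starters is the stayers' mean plus (k/18) × D, so leaving these women out understates the worsening by (k/18) × D. Both k and D are assumptions.

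| k | k/18 | D = 0.5 | D = 1 | D = 1.5 | D = 2 |
|---|---|---|---|---|---|
| 1 | 6% | 0.03 | 0.06 | 0.08 | 0.11 |
| 2 | 11% | 0.06 | 0.11 | 0.17 | 0.22 |
| 3 | 17% | 0.08 | 0.17 | 0.25 | 0.33 |
| 4 | 22% | 0.11 | 0.22 | 0.33 | 0.44 |

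If all k left within 3 months and were replaced, the starters would number 18 + k. The range would then run from 1/19 × 0.5 = 0.03 to 4/22 × 2 = 0.36 SD.

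**Chance that it arises at all**

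For an assumed probability p of leaving before month 6, the chance of at least one such woman in 18 is 1 − (1 − p)^18: 60% for p = 5%, 85% for p = 10%, 98% for p = 20%.

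**The case against.** The strongest reply is that tolerability does not rest on these forms. MENQOL, BD-II and SF-36 are exploratory. The secondary outcome is adverse-event incidence, adverse events are recorded at months 3 and 21, and a phone call "takes place one month after first leuprorelin injection". Complaints that make a woman leave can be captured there. This stands, and it limits the point to the questionnaire results. It is not a full answer. Adverse-event counts do not grade symptom burden or mood on a validated scale. Because intention to treat governs all analyses, the 3-month exclusion may also remove the same women from the adverse-event comparison.

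A reader might infer that every woman who stops early lacks an on-treatment score. The documents do not support that. Those who stop the drug but stay in the trial are still sent the month-6 forms. Those who leave after month 3 have an end-of-treatment step that may include questionnaires, a detail a condensed article can leave to the full protocol.

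A reader might also take month 3 as a stopping rule, so that only women who passed it answer at month 6. The text makes tolerance a condition for changing the injection interval, and the forms go to patients without that condition.

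The direction and size are assumed, too. The case of 4 in 18 places about the whole planned 20% drop-out before month 6 and attributes it to complaints, and losses in the delayed arm are also plausible. With 18 per arm the standard error of a difference in means is √(2/18) = 0.33 SD, so most of the tabulated shifts are smaller than the sampling error. That makes the shift hard to see in the data but does not remove it.

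Finally, a month-3 form alone would not reach women who leave before month 3. That is correct, and the change has to cover exit and the analysis set as well.

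**Conclusion.** The point holds in a limited form. The protocol's sections agree that no questionnaire is sent in the first 6 months after leuprorelin starts, in either arm, although tolerance is judged at 3 months. For direct starters who leave the trial before month 3, the lack of an on-treatment score follows from the stated schedule, and the withdrawal rule removes them from the analysed set. For those who leave between months 3 and 6, it depends on what the early end-of-treatment step contains.

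If these women fare worse, the treated arm's exploratory questionnaire results look too favourable, by about 0.03 to 0.44 SD over the assumed range. No single value within it can be defended from the document. A claim that the drug's tolerability as a whole will be overstated goes further than the text allows, because adverse events are collected in the same window. This is an inexpensive improvement to exploratory measures; it does not touch the primary outcome or the sample size.

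**What to change.** - Send MENQOL and BD-II at the existing month-3 visit in both arms, at the month-21 visit (3 months after the delayed start), and at any early stop of treatment or exit from the trial, including exits within the first 3 months.
- State that every randomised woman who started treatment stays in the tolerability and adverse-event analyses, whatever the replacement rule does to the intention-to-treat set. For comparisons between arms, keep women who leave the delayed arm early on the same terms. Without this, a score taken at exit before month 3 would be collected and then not used.
- Report the month-3 change between arms as an exploratory tolerability comparison.

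The cost is two digital forms that the trial already uses, mostly at visits that already exist, and a few minutes of patient time. No added visit and no change in sample size is needed.
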